**Figure 1 figure1:**
[figure not shown]
Flow of participants through the trial with a delayed intervention randomized waitlist-controlled design. N-ACT: neurobehavioral affective control training. Assessments are indicated in gray.

Hypotheses and analyses were preregistered at OSF. We plan to detail any changes to this protocol in future publications and disseminate our findings to the scientific community in accordance with the CONSORT-EHEALTH (Consolidated Standards of Reporting Trials of Electronic and Mobile Health Applications and Online Telehealth) checklist (V 1.6.1) [64].

### Ethical Considerations

The University of California Berkeley Committee for Protection of Human Subjects granted approval for this research (2023-01-15949) before data collection. All participants will complete written informed consent before commencing study procedures.

Participants will be assigned an ID number, which will be used in place of their name or other identifying information on all research materials. Data will be kept in secure, password-protected files. Although we plan to make data publicly available for reanalysis, we will carefully deidentify data before doing so. In publishing or presenting the results, we will not provide any information that could identify an individual participant.

Participants will receive course credit or monetary compensation for completing assessment procedures but will not be paid for time spent on screening or the intervention itself. Students will be able to earn credit toward required research hours in their psychology classes. We plan to increase the hourly payment rate slightly over the course of the trial to promote retention, from US $20/h for the baseline assessment to US $30/h for the postwaitlist and postintervention assessments. We will compensate participants up to US $60 (or 3 h of course credit) for completing the baseline assessment (2.5-h in-person session plus 30 min of questionnaires), a US $10 “bonus” for performance on an unrelated computer task during the baseline session, US $10 for each week of EMA if they complete at least 75% of the prompts, and US $60 for the postintervention assessment (1.5-h in-person session plus 30 min of questionnaires). Those randomized to the waitlist control condition will be eligible to receive up to an additional US $60 for completing the postwaitlist assessment (identical to the postintervention assessment).

In sum, participants assigned to complete N-ACT without the waitlist can earn up to US $150 (or 3 h of course credit plus up to US $90), while those in the waitlist control condition could earn up to US $70 in addition to those amounts. Payments will be prorated if participants complete only part of an assessment. We will remunerate participants within 1 week of each completed assessment via digital credit cards, which will be replenished as necessary.

### Study Procedures

#### Recruitment and Screening

We will invite up to 500 adults to complete preliminary screening procedures and an estimated 100 participants to complete the initial baseline assessment session. After accounting for 20% expected attrition, we expect 40 participants in each condition to complete all study procedures.

Study advertisements will be posted locally in public spaces and distributed by web (eg, via email listserves, Craigslist, and social media sites). We will also administer a prescreening survey to students enrolled in psychology classes at the University of California Berkeley, and we will invite students who meet the preliminary inclusion criteria based on those responses to take part in the study. Potential participants (recruited either from the community or from the student participant pool) will be directed to our website, where they can view additional details about the trial. We intend to recruit only secondarily from the student participant pool to supplement community-based recruitment, which will constitute most of the targeted sample. All questionnaires, including screening items, will be administered through REDCap (Research Electronic Data Capture; Vanderbilt University) software [65], which will also be used for the secure storage of collected data.

After providing informed consent, interested individuals will complete the brief web-based screening via REDCap to assess preliminary eligibility. The inclusion and exclusion criteria are presented in Textbox 1.

Inclusion and exclusion criteria.
**Inclusion criteria**
Current California residencyAge 18 to 65 yElevated scores on self-report measures of rumination (Mn >2 on the Brooding subscale of the Ruminative Responses Scale [13]) or emotion-related impulsivity (Mn >3 on the Feelings Trigger Action factor of the Three-Factor Impulsivity Index [9])
**Exclusion criteria**
Insufficient English literacy to understand study procedures (as assessed by self-report) or careless responding as indicated by the following:Failing ≥50% of the attention check items embedded in the screening questionnairesOverly rapid responding (ie, mean response time of <2 s for multiple-choice items)Qualitative review of long strings of identical entriesPositive history of brain tumors, neurological disorders, or head injuries accompanied by the following:Loss of consciousness of >5 min>2 separate instances of clinically significant head traumaRecent alcohol or other substance use disorder (in the past 6 mo) or current psychosis (in the past 2 wk) according to the Psychiatric Diagnostic Screening Questionnaire [66]Past-month active suicidal ideation paired with either of the following:An identified method, specific plan, or intentLifetime history of suicide attempts as assessed by the screen version of the Columbia Suicide Severity Rating Scale [67]

The exclusion criteria do not cover the presence of anxiety, depression, or other psychiatric symptoms, given our intention to target emotion dysregulation broadly and to assess the generalizability of effects across psychiatric diagnoses and severity, including participants with few or no symptoms and those without treatment history. However, the screening will include items from the self-rated screen version of the Columbia Suicide Severity Rating Scale (C-SSRS; for suicidal thoughts) as well as the alcohol, substance, and psychosis subscales from the Psychiatric Diagnostic Screening Questionnaire (PDSQ) [66]. Individuals who do not respond to the requisite screening items or do not meet eligibility requirements, including those whose responses to the psychiatric screening questions surpass established clinical thresholds, will be automatically informed that they will not be able to join the trial and will receive a list of mental health resources along with an invitation to contact our team should they desire additional referral assistance. We will provide further support for engaging with psychiatric care providers to respondents who endorse past-month active suicidal ideation with an identified method, specific plan, or intent on the C-SSRS.

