#### Risk Management

##### Overview

Trial procedures are designed to balance respect for participants’ autonomy with the need for safety. Study consent forms will provide contact information for crisis hotlines and other mental health resources. We will offer referral assistance to interested individuals. All team members with direct participant contact will receive training regarding psychiatric emergencies, suicide risk assessment, and crisis management. A detailed manual will provide assessment probes, decision rules, referral resources, and contact information for use during emergency situations. Training will emphasize procedures for providing feedback in a clinically sensitive manner, and senior investigators will use role-play to demonstrate fundamental principles related to assessment, obtaining supervision, providing referrals, and preparing documentation according to legal and ethical guidelines. This training will cover circumstances in which staff are permitted to breach confidentiality to contact emergency services.

Research assistants and coaches will be trained to carefully monitor cues indicating participant distress or discomfort, and we will offer breaks or opportunities to reschedule as warranted for fatigue or distress. Participants who endorse significant distress or endorse active suicidal ideation will be given the opportunity to speak with clinically licensed senior investigators, who will evaluate and determine the need for further follow-up. Research staff will work with these participants to develop a plan to obtain support, which may include strategies for discussing symptoms with their current provider, removing access to lethal means, and the provision of feedback or referrals. Our team has developed relationships with local sites to facilitate referral for individuals with insurance or those without; after referral, we will follow up with these participants as warranted to ensure that they received sufficient support.

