###### C-SSRS, Screen Version

The screening includes the self-report screen version of the C-SSRS [67], a well-validated and widely used instrument designed to assess suicidal thoughts and behaviors. Endorsement of the C-SSRS ideation item (Have you actually had any thoughts of killing yourself?) will trigger 3 follow-up items, to cover past-month presence of an identified method, intent, and a specific plan. Responding affirmatively to any of these 3 items will result in automatic study exclusion. Regardless of their responses, all participants will be asked an item to evaluate lifetime history of suicidal behavior; those who endorse this item in addition to past-month active suicidal ideation will also be automatically excluded from study participation.

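### The rule for further support at screening covers one of the two suicide-risk exclusions and does not name active ideation with a lifetime attempt

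*Protocol article*

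**What the plan says.** Textbox 1 of the protocol article has one suicide-risk exclusion with two branches, and both require active ideation in the past month. Branch (a) adds an identified method, a specific plan or intent. Branch (b) adds a lifetime history of suicide attempts.

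The section on the C-SSRS, Screen Version (under Measures, Screening) gives the item logic. Endorsing the ideation item "will trigger 3 follow-up items, to cover past-month presence of an identified method, intent, and a specific plan", and a yes to any of these excludes. The lifetime item is put to everyone: "Regardless of their responses, all participants will be asked an item to evaluate lifetime history of suicidal behavior". On branch (b), "those who endorse this item in addition to past-month active suicidal ideation will also be automatically excluded from study participation".

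The text after Textbox 1 sets two levels of response at screening. Every ineligible respondent "will receive a list of mental health resources along with an invitation to contact our team should they desire additional referral assistance". A second sentence adds more for some: "We will provide further support for engaging with psychiatric care providers to respondents who endorse past-month active suicidal ideation with an identified method". It continues with plan and intent and stops there.

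The Risk Management overview adds general provisions: "Study consent forms will provide contact information for crisis hotlines and other mental health resources" and "We will offer referral assistance to interested individuals". It also lets participants who report active suicidal ideation speak with a licensed senior investigator, and it refers to a manual with decision rules that is not shown.

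**The concern.** The exclusion rule and the further-support rule sit next to each other and use the same instrument, but the second repeats only the first branch of the exclusion. The plan treats current ideation with a past attempt as serious enough for automatic exclusion. The response that the screening text states for that respondent is nevertheless the one given to someone excluded for a low rumination score, and the respondent has to make the contact. Because the item covers the whole lifetime, the unnamed branch can include recent attempts. Screening is web-based and notification of ineligibility is automatic, so the article describes no staff contact at that step that would close the gap.

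The safety of people screened out is at stake. The estimand, the power and the analysis are not affected.

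**Working it through.** The plan gives no figure to reproduce. The check sets the two rules side by side and counts the answer patterns that each covers.

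**Inputs** (C-SSRS, Screen Version section and the text after Textbox 1)
- Ideation item endorsed.
- Three yes/no follow-ups: method, intent, plan.
- One yes/no lifetime item, asked of all.
- Exclusion if any follow-up is yes (branch a), or if the lifetime item is yes together with ideation (branch b).
- Further support if ideation comes with method, plan or intent.

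**Count, given ideation endorsed**
- All patterns: 2^3 × 2 = 16.
- Branch (a), at least one follow-up yes: (8 − 1) × 2 = 14.
- Branch (b) without (a), all follow-ups no and lifetime item yes: 1 × 1 = 1.
- Not excluded on this criterion, all four items no: 1 × 1 = 1.
- Excluded: 14 + 1 = 15.
- Named in the further-support sentence: 14.
- Excluded but not named: 15 − 14 = 1.

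A respondent who meets both branches is covered through (a). The gap is therefore exactly the respondent with ideation and a lifetime attempt but no method, intent or plan.

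**Does other text reach this respondent?**
- The list and invitation go to all ineligible respondents.
- The crisis contacts in the consent form and the referral assistance are general and add nothing specific to branch (b).
- The conversation with a licensed investigator is triggered by active ideation, which branch (b) always includes. It stands beside text on staff watching for distress and offering breaks or rescheduling, which describes people attending sessions. It does not mention people excluded at the web screen.

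**Workload.** The article states: "We will invite up to 500 adults to complete preliminary screening procedures". At that ceiling, each 1% of respondents with the unnamed pattern means 0.01 × 500 = 5 extra contacts at most. The documents give no rate for the pattern, so this is a conversion and not an estimate.

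**The case against.** The strongest case on the other side has four parts.

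1. **Deliberate tiering.** Exclusion decides who is suitable for the trial, while outreach can reasonably be tied to current acuity. A list and offered help for all, with more for those with a method, plan or intent, is a coherent scheme. This stands as a possible reason, although the article does not give it. The proposed wording can keep the tiering.

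2. **Risk Management may already cover branch (b).** The C-SSRS section calls screening respondents participants, consent is obtained before the web screen, and Table 1 schedules the C-SSRS at screening only. An offer to participants who report active ideation could therefore include them. This part stands, and it limits the point. A reader might infer that branch (b) respondents get nothing beyond the list and invitation. The documents do not support so firm a statement. The narrower reading is still the more natural one. The offer sits among provisions for sessions, and if it covered everyone screened out, the separate screening rule would be largely redundant.

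3. **The manual is not shown.** It may set rules for branch (b). That is true, but the point is not about a detail left to another document. The article itself states a trigger, and that trigger is narrower than its own exclusion rule.

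4. **Why stop at branch (b)?** Respondents with ideation alone who are excluded for another reason are promised the same list and invitation. That is correct. The difference is that the plan does not treat ideation alone as an excluding suicide risk.

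A reader might also infer that the article contradicts itself between screening and Risk Management. It does not, because the two passages can apply to different groups or overlap without conflict.

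**Conclusion.** The point holds in a limited form. The only further-support rule specific to screening is triggered by ideation with a method, plan or intent, and it does not name ideation with a lifetime attempt. On that text, respondents in the second branch alone are promised what every ineligible respondent is promised. Whether the Risk Management offer extends to them is left open.

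The size is small: one of 15 excluded patterns. That fraction should not be read as a share of people or of risk, since the patterns are not equally likely and no rate is given. The conclusion rests on the item logic as printed and on reading the further-support sentence as a complete statement of its trigger. It is a cheap, optional improvement in participant safety, with no bearing on the analysis.

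**What to change.** Reword the further-support sentence after Textbox 1 so that help in engaging with psychiatric care goes to respondents who report active ideation in the past month and are excluded under either suicide-risk criterion. If tiering by acuity is wanted, add that those with a method, plan or intent are contacted first. If the licensed-investigator offer under Risk Management is meant to cover people excluded at the web screen, say so there too.

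The cost is one sentence and one added condition. The automatic exclusion already has to detect the branch (b) combination, and the referral procedures exist. The article does not say how contact details are held at the web screen, but the support already promised to branch (a) implies some route. The downside is a small number of extra contacts. According to the article, recruitment had not yet begun at publication, so the change could be made before the first screen.

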#### Assessment

##### Overview

Each in-person assessment session will involve core measures expected to take 90 minutes, including a battery of computer-based behavioral tasks measuring cold and hot executive functions as well as the Positive and Negative Affect Schedule (PANAS) [68] to evaluate subjective mood before and after the neuropsychological examination. Within 24 hours of each session, participants will be asked to complete self-rated questionnaires to evaluate psychiatric symptoms and other variables of interest, which will require an additional 30 to 40 minutes. Table 1 presents key measures included at each assessment and intervention time point (refer to Multimedia Appendix 1 for a comprehensive list and additional details).

**Table 1 table1:** Administration schedule of core measuresa.

Domains and measures			Format		Screening		Baseline assessment		Postwaitlist assessment	N-ACT^a^ assessment		Post–N-ACT assessment
**Emotion dysregulation**												
	Ruminative Responses Scale–Brooding	Self-report		✓				✓			✓	
	Three-Factor Impulsivity Index–Feelings Trigger Action	Self-report		✓				✓			✓	
	Three-Factor Impulsivity Index–Pervasive Influence of Feelings	Self-report				✓		✓			✓	
**Psychiatric symptom severity**												
	Columbia Suicide Severity Rating Scale	Self-report		✓								
	Demographic questionnaire or mental health history survey	Self-report		✓								
	Psychiatric Diagnostic Screening Questionnaire–Alcohol Use Disorder or Substance Use Disorder or Psychosis	Self-report		✓								
	Externalizing Spectrum Inventory–Revised	Self-report				✓		✓			✓	
	Inventory of Depression and Anxiety Symptoms, Expanded Version	Self-report				✓		✓			✓	
**Neuropsychological assessment battery**												
	Digit Span Backward	Behavioral				✓		✓			✓	
	Stop-signal task	Behavioral				✓		✓			✓	
	Trail-making test	Behavioral				✓		✓			✓	
	Wechsler Adult Intelligence Scale, Fourth Edition–Vocabulary	Interview				✓		✓			✓	
	Emotional stop-signal task	Behavioral				✓		✓			✓	
	Memory and affective flexibility task	Behavioral				✓		✓			✓	
**Affective control training (N-ACT)**												
	Adaptive emotional n*-*back task	Behavioral								✓		
	Emotional stop-signal task–adaptive	Behavioral								✓		

^a^A comprehensive list of secondary measures and additional outcomes is available in Multimedia Appendix 1.

##### Neuropsychological Battery

At each assessment session, participants will perform 5 computerized neuropsychological tasks (in a pseudorandom order) to index the hypothesized effects of N-ACT on emotional working memory and emotional response inhibition as well as the transfer of targeted inhibitory control processes from T1 (baseline time point) to T2 (postwaitlist or postintervention time point). The assessment battery accordingly includes 3 widely used gold standard cold executive functioning tasks that measure key components of cognitive control: (1) Digit Span Backward [69], a working memory test that requires participants to select (using the computer cursor) a series of numbers in the opposite order from which the digits were presented (in numerical strings of increasing length); (2) the stop-signal task (SST) [70], a measure of prepotent response inhibition in which participants must quickly indicate (via keypress) the direction of rapidly presented arrow stimuli, except on trials that include an unpredictable buzzer tone, which require termination of the initiated motor response; and (3) the trail-making test [71], an assay of set-shifting or task-switching ability that involves using the computer cursor to draw a path connecting an array of alphanumeric stimuli in an alternating sequential pattern (eg, “A” to “1” to “B” to “2,” and so on) as quickly as possible. The neuropsychological battery additionally includes the administration of the Vocabulary subtest from the Wechsler Adult Intelligence Scale, Fourth Edition [72], to assess crystallized intelligence, which we will examine in exploratory analyses of the specificity of intervention effects.

Participants will also complete 2 tasks to confirm the efficacy of N-ACT in augmenting 2 core facets of affective control, emotional response inhibition and emotional working memory: (1) the ESST [37,39,43], which follows procedures parallel to those of the traditional SST but differs in that participants must rapidly categorize affective pictures according to perceived valence (ie, “positive or pleasant” vs “negative or unpleasant”) instead of indicating the direction of arrow stimuli, while still inhibiting prepotent motor responses on a subset of trials with an unpredictable auditory stop signal (buzzer or tone); and (2) the memory and affective flexibility task (MAFT) [73], a novel modified n-back procedure that provides indices of emotional working memory as well as affective flexibility (as captured by emotional set shifting or task switching trials) by asking participants to recall whether they have previously seen (1-3 trials earlier) serially presented images with affective content (ie, “n-level,” which varies by block), with occasional interspersed “switch” trials prompting them to respond instead to perceived image valence (identical to ESST go or no-signal trials).

##### Psychophysiology

During the administration of the computerized cognitive assessment tasks, we will gather 2 metrics of arousal—pupil dilation, which reflects phasic norepinephrine signaling; and skin conductance, an index of autonomic sympathetic nervous system activity—to evaluate the physiological correlates of cold and hot executive functioning. We will consider incorporating physiological reactivity variables gathered during the latter set of tasks as secondary indicators in exploratory mechanistic analyses of the hypothesized treatment effects (Multimedia Appendix 1).

Pupil measurements will be recorded noninvasively with a Tobii T-120 infrared eye tracker [74] using E-Prime Extensions for Tobii [75]. We will not gather pupillometry data from participants who report a history of epilepsy or seizures triggered by arcade or video games, computer or television screens, or flickering fluorescent bulbs. Skin conductance levels will be monitored by electrodes placed (by the participant) on the inner sole of the foot. Trained research staff will calibrate physiological recording hardware (eg, by ensuring proper electrode placement and adjusting a chin rest to limit movement-related artifacts) for maximum comfort and signal.

